#### Multivariate analysis

##### Subgroup analyses

The analyses described above will also be performed separately for patients who fulfil the Rome III IBS diagnostic criteria for constipation-predominant, diarrhoea-predominant and mixed type IBS. In a study of Gonsakorale et al [35] one of the conclusions was that hypnotherapy was less useful for males with diarrhoea. If males with diarrhoea-predominant bowel habit are over-represented in one of the conditions, adjustment in multivariate regression analysis is indicated.

Analyses will be performed separately for those referred from primary and secondary health care. In secondary care, IBS-patients have a longer disease history, more psychosocial co-morbidity and higher stress and depression scores. It is possible that these differences may influence the effect of the intervention.

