### Sample Size Calculation

Assuming an individual hypnotherapy response rate of 57% [2], a maximum acceptable level of difference of 15% between individual and group hypnotherapy, an alpha of 0.05 and power (1-beta) of 0.80, 135 patients are required in both arms of the non-inferiority trial to show that group-hypnotherapy is not inferior to individual hypnotherapy.

Spiller [34], in an overview of 25 randomised controlled trials, states that when the placebo response is plotted against the length of study, placebo response will be maximum of 75% at around 6-8 weeks, falling to 25% at 24 weeks and zero at 12 months. Our follow-up period will be 9 months. To test whether group hypnotherapy is more effective than group placebo therapy, we will have more than sufficient power assuming a placebo-response rate of 25% and a group hypnotherapy response rate of 57% [13] using the proposed 135 patients in both arms. Powering the study for only the comparison between hypnotherapy and the control intervention, would require only 44 patients in both arms assuming an alpha of 0.05, a power (1-beta) of 0.80, a cluster size of 6 patients per therapist and an intra-class correlation coefficient of 0.05. Assuming at least 10% of loss to follow-up, 354 patients need to be included in the study (150+150+54 (placebo-arm)).

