#### Uni- & bivariate analysis

The percentage of patients with a positive response will be calculated post-treatment and at 9 months after treatment and differences between the three randomisation arms will be tested with the chi-square test.

In addition, the adequate relief scores and secondary outcomes (IBS- SSS, IBS-QoL, SCL-90-, CS- FBD-, SES- and TiC-P scores) will be estimated by time point of assessment and arm of randomisation using a statistical model for repeated measurements (preferably a random effects model). To assess the difference between the arms of randomisation by time point of assessment, terms for interaction of {arm × time point} will be included in the statistical model.

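### Subgroup analyses are repeated separately by IBS subtype and care setting with no arm-by-subgroup interaction, so they cannot show whether the effect differs between subgroups

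*Protocol article*

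**What the plan says.** The Uni- & bivariate analysis section sets two analyses. For the responder percentage, after treatment and at 9 months, "differences between the three randomisation arms will be tested with the chi-square test". For the adequate relief scores and secondary outcomes there is a repeated-measures model in which "terms for interaction of {arm × time point} will be included in the statistical model".

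The Subgroup analyses section carries both into subgroups. On constipation-predominant, diarrhoea-predominant and mixed IBS: "The analyses described above will also be performed separately for patients who fulfil the Rome III IBS diagnostic criteria". On referral source: "Analyses will be performed separately for those referred from primary and secondary health care". The care-setting paragraph notes that secondary-care patients have a longer history and more psychosocial burden, and concludes: "It is possible that these differences may influence the effect of the intervention".

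Two regression adjustments are also described: one if males with diarrhoea-predominant habit are over-represented in an arm, and one for baseline differences in general (Adjustment for confounders).

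**The concern.** The reason given for splitting by care setting is effect modification: does the benefit of hypnotherapy depend on where the patient was referred from? A test within primary care and another within secondary care each ask whether there is an effect in that stratum. Neither asks whether the two effects differ. Subgroups of different size, or of equal size with modest power, will often fall on opposite sides of 0.05 when the true effect is the same.

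The only interaction in the article, arm by time point, compares arms over time and not effects between subgroups. The regression adjustments deal with imbalance and confounding. The published result that the article cites for males with diarrhoea, a lesser benefit, describes a differing effect, yet the response to it is adjustment for imbalance, which does not examine that either.

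At stake is a report that hypnotherapy works in one subtype or setting and not in another when the data contain no evidence of a difference. The control arm is small (54 randomised), so each subgroup comparison rests on few control patients.

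**Working it through.** **Inputs from Sample Size Calculation.** Hypnotherapy response 57%, control response 25%; 150 + 150 + 54 = 354 randomised; 10% loss; cluster size 6 and intra-class correlation 0.05. Evaluable: 150 × 0.9 = 135 per hypnotherapy arm and 54 × 0.9 = 48.6, about 49 controls. Design effect: 1 + (6 − 1) × 0.05 = 1.25.

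**The plan's own figures.** Non-inferiority, one-sided 0.05, 80% power: (1.645 + 0.842)² × 2 × 0.57 × 0.43 / 0.15² = 134.7, so 135 as stated. Superiority: 36 per arm (two-sided, pooled variance) × 1.25 = 45, against 44 stated. One-sided with continuity correction gives 35 × 1.25 = 43.75, so 44. The sample size is not at issue here.

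**Assumptions.** Subgroup shares are not given, so equal splits are taken first and then varied. The true effect is identical in every subgroup, the test is two-sided at 0.05, and subgroups are independent.

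**Power within a subgroup** (group hypnotherapy versus control, pooled variance as in a chi-square test): Φ{(0.32 − 1.96 × SE₀) / SE₁}, where SE₀ uses the pooled rate (135 × 0.57 + 49 × 0.25) / 184 = 0.485 and SE₁ uses the separate rates.

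| Comparison | n | SE₀ | SE₁ | Power |
|---|---|---|---|---|
| Whole trial | 135 vs 49 | 0.0834 | 0.0751 | 98% |
| One third (subtype) | 45 vs 16.3 | 0.1444 | 0.1301 | 61% |
| One third, design effect 1.25 | same | 0.1614 | 0.1455 | 51% |
| One half (setting) | 67.5 vs 24.5 | 0.1179 | 0.1062 | 80% |
| One half, design effect 1.25 | same | 0.1318 | 0.1188 | 70% |

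**Chance that subgroups disagree on significance**, with power w:

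- Three subtypes, 1 − w³ − (1 − w)³. With w = 0.612: 1 − 0.229 − 0.058 = 0.71. With w = 0.510: 1 − 0.133 − 0.118 = 0.75.
- Two settings, 2w(1 − w). With w = 0.799: 0.32. With w = 0.698: 0.42.

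**Three-arm test.** The plan names a chi-square test across three arms. Simulating that test (200,000 runs, no clustering, equal splits) gives 73% for subtypes and 36% for settings.

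**Sensitivity (no design effect).**

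- Subtypes split 50/30/20: powers 80%, 56% and 39%, disagreement 77%.
- Settings split 70/30: powers 92% and 56%, disagreement 45%.
- Control response 37.5%, one of the placebo rates cited under Placebo effect: 59% (equal thirds) and 47% (equal halves).
- Control response 47%, the other rate cited there: 28% and 23%. Disagreement falls because power is so low that mostly nothing is significant.

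**No effect anywhere.** At least one false positive: 1 − 0.95³ = 14.3% over three subtypes and 1 − 0.95² = 9.8% over two settings, per outcome and time point.

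**Comparator.** A heterogeneity test on log odds ratios, simulated with the same identical effect (57% versus 25%), declares a subgroup difference in about 2.5% of trials for subtypes and 3.4–4.0% for settings, against a nominal 5%.

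**The case against.** The best defence is that separate analysis is not itself a mistake. The repeated analyses include response percentages and model estimates by arm and time point, and tabulating these within subgroups is legitimate description. An interaction test could be added in a full protocol or analysis plan that is not shown, and it would have low power at this size. All of that is true. It does not remove the point: the article goes beyond silence. It fixes separate analysis as its subgroup method and, for care setting, states a question that this method cannot answer.

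Several stronger readings are tempting and should not be made:

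- A reader might infer that effect modification is the stated purpose for subtype as well. The sentence about influencing the effect belongs to the care-setting paragraph only; for subtype the purpose has to be inferred.
- A reader might infer that the plan intends to judge subgroups by comparing p-values. It does not say so. The risk arises because no other comparison is offered.
- A reader might infer that false subgroup differences are certain. They are a probability under assumed splits. For two equal settings, agreement is the more likely result (58–68%).
- A reader might infer that subgroup effects are among the trial's aims. The Aims and Hypotheses sections mention neither subtype nor care setting.
- A reader might extend the argument to non-inferiority within subgroups. The analysis section lists no non-inferiority test among those to be repeated, so that does not follow.

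**Conclusion.** The point holds as a fault in the stated subgroup method. It does not touch the primary comparisons. With an identical effect in every subgroup, significance would disagree in about 71–75% of trials across three equal subtypes and 32–42% across two equal care settings, per outcome and time point. The two ends of each range are without and with the design effect of 1.25. Members of one therapy group may be spread over several subtypes, so 1.25 is probably an upper value for that split.

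The figures rest on the plan's 57% and 25%, on 135 versus about 49 evaluable patients, and on assumed shares. The uneven splits tried give more disagreement. Higher control rates generally give less for subtypes (59% and 28%); for settings they give 47% and then 23%. The qualitative conclusion depends on none of these values: separate tests do not assess whether effects differ.

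**What to change.** Replace the separate testing in the Subgroup analyses section as follows. For each outcome, fit a model in all randomised patients that includes arm-by-care-setting and arm-by-subtype terms. Report the effect estimate with confidence interval in each subgroup together with the interaction p-value. State that these analyses are exploratory and have low power to detect a true difference, and that no conclusion about differing effects will be drawn from significance or non-significance within a subgroup. If an unseen analysis plan already does this, align the article's text with it.

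The change needs no further patients or data. It costs slightly more analysis work and the loss of some statements that hypnotherapy was significant in a given subgroup.

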#### Adjustment for confounders

In case of (unexpected) differences in relevant baseline characteristics between the three comparison groups, adjustment for the possible confounding effect of these differences will be performed in multivariate regression analyses.

### Risk/Benefit for patients

Benefit: Research indicates that hypnotherapy is a promising intervention for IBS which could potentially be of considerable benefit to the patients participating in the study. Research also indicates that patients want to be informed more about IBS. Patients randomised to the placebo condition receive this information and thus can also benefit from participating in the study.

Risk: In all the research that has been evaluated by the Cochrane study, no adverse effects for patients have been reported. This treatment is symptom-oriented with care taken to exclude those individuals with contra-indications and treatment is always carried out by experienced therapists educated in hypnotherapy.

## Discussion; Methodological challenges

In planning this study, a number of challenges commonly encountered in studies on functional GI diseases needed to be overcome: selection of the study population; diagnostic inclusion criteria; a valid control intervention; placebo effect and outcome assessment.

### Selection of the study population

Lack of heterogeneity among IBS patients can affect the generalisability of trial results [36]. To overcome this problem, patients will be recruited from primary and secondary care populations. The NICE guideline (2008) recommends the inclusion of patients from primary care to enhance the generalisability of the results. Co-operating hospitals and primary care practices are situated all over Holland, so the population participating in the study will be representative of the whole Dutch population.

Although attention to the study was drawn by announcements to both physicians in primary and secondary care and patients by the Dutch IBS Patient Foundation web-site, there will always be a selection bias, because only patients who are motivated are included in this study. It cannot be ruled out that they differ in some respects from those who do not want to participate on the effect of hypnotherapy.

### Diagnostic inclusion criteria

The selection of the diagnostic inclusion criteria were a second challenge in the study. A task force of the American Journal of Gastroenterology [37] conducted a systematic review on the accuracy of symptom-based criteria in the diagnosis of IBS. They summarise the diagnostic criteria that have been used over the years which are those reported by: Manning (1978); Kruis (1984) Rome I (1990); Rome II (1999) Rome III (2006). The main differences are in the number of symptoms included as well as their duration which is important as they should be been present for a considerable period of time before the diagnosis is considered.

The accuracy of the Rome II and III criteria has not been formally evaluated yet and the ACG task force chose their own pragmatic definition: "abdominal pain or discomfort that occurs in association with altered bowel habits over a period of at least three months".

Because of the problem of the absence of a specific diagnostic test for IBS, the Rome committee developed the IBS-module, a short questionnaire (10 questions) with a scoring device. It is applicable in primary and secondary care and takes only a few minutes for patients to complete. For standardisation and to facilitate comparison of research populations in the future, in this RCT the questionnaire was chosen to confirm the diagnosis of IBS.

The Rome committee has started a translation project to make it possible for this questionnaire to be used worldwide. Following official translation guidelines [38] and with the official consent of the Rome III committee, the module has been translated into Dutch and will be of use to every specialist in the field of IBS in the Netherlands.

### Optimal control intervention

To design a good control intervention is notoriously difficult in research on the effectiveness of psychological treatments [39]. "Care as usual "is not a good control-option since it does not exclude the possibility that treatment effect is due to differences in therapist attention rather than to the intervention [23]. A good placebo condition needs to have all components of the experimental intervention, except the active component. This is very difficult to realise with psychotherapeutic interventions. A "sham" intervention with the same time investment for patient and therapist but with a non therapeutic intervention, potentially generates a negative effect. Consequently, an intervention was designed in which hypnotherapy was missing but all other components were retained: time, attention, active intervention and contact with therapist. The intervention, an informative educational programme, covers topics IBS patients like to have more knowledge about [18-22]. The informative educational programme will be given by nurse practitioners or welfare workers and not by hypnotherapists because it is anticipated that hypnotherapists will automatically use the suggestive language they use in the hypnotherapy. To emphasise the supportive and educational character of this control-intervention, the deliberate use of nurse practitioners or welfare workers was felt to be the most appropriate to deliver this intervention. Furthermore, the effects of the doctor-patient relationship will be controlled for by using multiple, experienced therapists [39].

### Placebo effect

The placebo response causes serious problems for the design of RCT's in IBS. Spiller (1999) describes on the basis of 25 RCTs on medication and fibre from 1976-1998, a median placebo response of 47% [34]. Ford & Moayyedi (2010) estimated a response rate of 37.5% across all RCT's on pharmacological therapies in adult IBS-patients [40]. Spiller claims that the placebo response diminishes after approximately 12 weeks and was lost altogether by 6 months. Recommendations to diminish the effect of placebo response on outcomes of RCT's are:

Lengths of the therapy should be more than 8 weeks and follow-up for more than 6 months; diagnosis should be based on the Rome-criteria and not on clinical judgement; patient-reported endpoints are better than physician-reported outcomes; it is important to be able to distinguish between subgroups of IBS-C, IBS-D and IBS-M.

In the design of this RCT these recommendations were met in terms of: the length of therapy is 3 months; follow up will be 9 months after ending the therapy and we chose for the Rome III IBS-module to diagnose the cases and distinguish the sub-groups.

### Outcome assessment

As no objective standards for diagnosing functional GI-diseases exist, outcome assessments have to be based on subjective criteria. According to Irvine [23] the "adequate relief" questionnaire [25] is the current standard primary outcome measurement in treatment trials of Functional Gastrointestinal Disorders. For a more detailed IBS symptom assessment the IBS-Severity Scoring System [27] is recommended [24]. Furthermore, IBS related Quality of Life is an important secondary outcome measure [23]. At present, the IBS-Quality of Life measurement [28] is the best choice, "because it has been the most extensively validated and shows appropriate psychometric quality" [24]. Mangel, (outcome measure:"adequate relief "[25]) and [name] (IBS-SSS [27]) gave their consent for translating these questionnaires into Dutch.

IBS-complaints can have an episodic course and in accord with the recommendation on measuring severity during episodic symptoms by the research design of the Rome committee [23], patients will fill in the assessments on two occasions: immediately at the end of treatment and after nine months. Also the 'adequate relief' question is asked every week, for a period of four weeks.

It is possible that the patients in the control group with educational supportive therapy also will experience some improvement in their complaints, but the expectation is that treatment with hypnotherapy will be superior.

### Conclusion

The results of this primary and secondary care based randomised placebo controlled trial, evaluating the efficacy of individual and group hypnotherapy treatment in IBS, will contribute to the scientific basis of IBS management. The trial intends to include the greatest population of patients of all the trials in psychological treatments for IBS to date [2,12].

If the results of the study show that (group) hypnotherapy for IBS is effective, implementation into clinical practice will be the next aim.
